##### **4.3. Study population**

The study will involve adolescents aged 10-14 years in their first year of secondary school in Copperbelt Province, Zambia. Adolescence is an important phase of life which marks transition from childhood to adulthood and oral health related behaviors acquired during this phase affect their current and future oral health. Adolescents' oral health status and related behaviors are directly dependent on their family's socio-economic status and therefore the effect of any socioeconomic gradient in health is likely to be reflected in this group.

#### 4.4. Sample size

A sample size of 1760 adolescents calculated using a Cluster Randomized Controlled Trial formula (RCT) and adjustment to account for design effect and 10% loss to follow up as shown below is expected to be sufficient for the study.

- (i) Sample size formula for RCT considering simple random sampling:

$$2N = \frac{4(Z_{\alpha} + Z_{\beta})^2 \sigma^2}{\delta^2}$$

Where

2N is number of participants in two arms

$Z_{\alpha}$  is point on standard normal distribution corresponding to level of confidence of the study estimated to be 1.96 for 95% Confidence Interval

$Z_{\beta}$  is value corresponding to 85% power of the study =1.03

$\sigma$  is known mean DMFT from a previous study in Ndola, Zambia by Nasilele et al (2018)=1.34

$\delta$  is the expected clinically significant change in mean DMFT set at 20% =0.268

Based on assumptions and known values above the sample size for 2 arms is calculated as follow:

$$2N = \frac{4(1.96+1.03)^2 (1.34)^2}{(0.268)^2}$$

$$2N = 894.01 = 894$$

- (ii) Sample size considering cluster design, hence adjusting for design effect

$$n_c = n_1 [1 + (m - 1) \rho]$$

$$n_c = 894 [1 + (80 - 1) 0.01]$$

$$n_c = \text{estimated to be } 1600.26 = 1600$$

Where

$n_c$  = Number of pupils/participants in cluster per arm

$n_1$  = Individual number of participants (pupils) in an arm when considering random sampling

$\rho$  = Estimated intra-cluster correlation coefficient (ICC) to be 0.01

$m$  = Estimated cluster size in this study is 80 students in a class

- (iii) Sample size adjustment to consider loss to follow up assumed at 10%

$$n_c = 1600 + \{1600 \times (10/100)\} = 1760$$

$$\text{Final minimum sample size considered} = 1760$$

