#### **4.5. Sampling**

A two-stage cluster sampling technique will be used; district being a sampling unit at stage one and secondary schools at stage two. Through simple random sampling, three out of ten districts of Copperbelt province will be selected and from each district a total of six clusters (secondary schools) will thereafter be selected as part of the study. To attain a sample size of 1,760 participants, 18 clusters with cluster size of 90-100 will be involved. All adolescents aged 10-14 in grade 8 at selected clusters will be eligible to participate in this study.

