#### **4.7. Randomization**

Allocation of clusters (secondary schools) into intervention and control groups will be done by stratified block randomization procedure whereby the district will be a stratifying unit and schools a blocking unit. Four randomly selected schools in the three districts will be listed in alphabetical order and assigned numbers 1 to 4. Computer random number generator will be used to randomly allocate 2 clusters in intervention and 2 in control groups in each district. The first two numbers generated will be allocated to intervention and the second two in control.

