#### **4.12. Data entry cleaning and analysis**

Data entry, coding and processing will be done using a computer software program IBM SPSS for Windows (Version 23). Frequency distribution for proportions, means (SD), cross tabulation with chi –square and binary logistic regression reported in odds ratio and 95% (CI) will be performed per respective objectives.

Frequency distribution for proportions of adolescents with plaque, gingival bleeding, poor oral health behaviors and oral health related quality of life. Dental caries experience will be summarized as number and percentage. Furthermore, cross tabulation for bivariate comparison of differences in intervention outcome variables by socio-demographics, study arms and oral health behaviors will be conducted. To examine for the differences between the groups (effectiveness of trial intervention) generalized estimating equations will be performed and reported in odds ratio and 95% confidence interval. A statistical significance difference shall be assumed when  $p \leq 0.05$ . Analysis plan per objective is summarized in appendix 6.

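### Section 4.4 claims 85% power at a two-sided 5% level from normal multipliers, although only 18 (or 12) schools are compared; with a t reference the power is about 78% for 18 schools

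*Protocol*

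**What the plan says.** Section 4.4 starts from a formula for two individually randomized arms. The confidence multiplier "is point on standard normal distribution corresponding to level of confidence of the study estimated to be 1.96 for 95% Confidence Interval", and the second multiplier "is value corresponding to 85% power of the study =1.03". The value entered as sigma, 1.34, is described as the "known mean DMFT from a previous study in Ndola, Zambia". The difference "is the expected clinically significant change in mean DMFT set at 20% =0.268". The result is multiplied by a design effect built from 80 pupils per cluster and an "Estimated intra-cluster correlation coefficient (ICC) to be 0.01", and 10% is added for loss, giving 1,760.

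Section 4.5 says that "18 clusters with cluster size of 90-100 will be involved". Section 4.7 works with four schools in each of three districts and will "randomly allocate 2 clusters in intervention and 2 in control groups in each district", which makes 12. Section 4.12 says that for the effect of the intervention "generalized estimating equations will be performed and reported in odds ratio and 95% confidence interval", with p ≤ 0.05 counted as significant. Nothing in the protocol allows for the small number of schools.

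**The concern.** A design effect enlarges the variance to reflect the likeness of pupils within a school. It does not deal with the fact that this variance is unknown and must be estimated from 9 schools against 9, or 6 against 6. The multipliers 1.96 and 1.03 treat it as known. With so few schools the correct critical value is visibly larger, so the stated power and the stated significance level cannot both hold. A test that keeps 5% has less power than Section 4.4 promises; a test that keeps 1.96 rejects a true null hypothesis more than 5% of the time, and a result just under p = 0.05 would be open to challenge.

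**Working it through.** **Inputs, all from the protocol.** Sigma 1.34 (taken as the SD, as 4.4 does), difference 0.268, ICC 0.01, cluster size 80, loss 10% (4.4); 18 schools (4.5) or 12 (4.7). The degrees of freedom are an assumption: schools − 2, or schools − 4 if two district terms are fitted.

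**Reproducing 4.4.**
- 2N = 4 × (1.96 + 1.03)² × 1.34² / 0.268² = 894.01
- Design effect = 1 + 79 × 0.01 = 1.79, and 894 × 1.79 = 1600.26
- 1600 × 1.10 = 1760

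Every step agrees with the protocol.

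**Formula for the check.** With k schools in all and m pupils analysed in each, the noncentrality is 0.268 / √(4 × 1.34² × [1 + (m − 1) × 0.01] / (k × m)). Power under z is Φ(noncentrality − 1.96). Power under t comes from the noncentral t distribution with the school degrees of freedom.

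**Step 1: change only the reference distribution.** The 1,600 pupils at 80 per school imply 20 schools and a noncentrality of 2.99, for which z gives 84.8%. Holding 2.99 fixed:

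| Schools | df | 5% critical value | Power |
|---|---|---|---|
| 20 | 18 | 2.101 | 80.7% |
| 18 | 16 | 2.120 | 80.1% |
| 18, district terms | 14 | 2.145 | 79.4% |
| 12 | 10 | 2.228 | 76.9% |
| 12, district terms | 8 | 2.306 | 74.5% |

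This isolates the fault: a loss of 4 to 5 points at 18 to 20 schools, and about 8 points at 12 (about 10 with district terms).

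**Step 2: the layout as planned, after 10% loss.** 1,760 × 0.9 = 1,584 pupils analysed, which is 88 per school for 18 schools and 132 for 12.

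| Layout | Noncentrality | Power, z | Power, t | Power, t, district terms |
|---|---|---|---|---|
| 18 × 88 | 2.910 | 82.9% | 78.0% | 77.2% |
| 12 × 132 | 2.619 | 74.5% | 65.6% | 63.2% |

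The fall from 85% to the z column comes from school size, number of schools and the loss allowance. Only the step from the z column to the t columns belongs to this point.

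**Step 3: can the stated layout recover 85%?** With 18 schools, 100 pupils analysed in each and no loss at all, power under t is 80.6%. Reading 4.4 as 1,760 / 80 = 22 schools, with 72 analysed in each after loss, gives 82.5% (20 df). Neither reaches 85%.

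**Step 4: the level if 1.96 is kept.** With an unbiased variance the true two-sided level is 2 × P(t > 1.96): 6.8% on 16 df and 7.8% on 10 df (7.0% and 8.6% on 14 and 8 df). With an uncorrected sandwich variance and equal school sizes, the effective cut-off for g schools per arm is 1.96 × √((g − 1)/g), that is 1.848 for g = 9 and 1.789 for g = 6, and the level is 8.3% or 10.4%. Simulation of 18 × 88 under those conditions gave 85.1% power at a level of 8.4%: there, the promised power returns only when the 5% level is exceeded.

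**The case against.** **The arithmetic is right, and normal multipliers with a design effect are a common approximation.** True: this is a fault of method, not a slip. With this few schools the approximation costs 4 to 8 points on 4.4's own inputs, which is enough to make the stated 85% wrong.

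**The fall to 78% or 66% is not all due to the multipliers.** This stands. A reader might take the whole gap from 85% as the price of z against t. The z column in Step 2 shows otherwise: for 18 schools about 5 points are due to the reference distribution, and for 12 schools roughly half of the fall is there before t is used.

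**Section 4.12 names no variance estimator or reference distribution, and such detail can sit in a statistical analysis plan.** This also stands. A reader might infer that the trial will run at an 8% or 10% false-positive rate. The protocol does not support that: those rates need an uncorrected sandwich variance, which it does not specify. The point rests on what 4.4 itself fixes, since either choice of test leaves one of its two figures wrong.

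**Repeated measurements could recover power.** Section 4.9.1 says that each adolescent's data will be paired. If baseline adjustment cut the variance at both levels by about 17% (a correlation of about 0.41, an assumption), 18 × 88 would reach 85% under t. But 4.4 takes no credit for this, so its figure does not follow from what it states.

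**Other inputs matter more, and the planned effect measure differs.** On 18 × 88 with t, assumed SDs from 1.2 to 1.6 give 86% down to 63%, and assumed ICCs from 0.005 to 0.02 give 88% down to 62%. In addition, 4.4 powers a mean difference while 4.12 reports odds ratios. These are fair reasons not to read 78% as precise. They do not restore 85% on the inputs that 4.4 gives.

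**Conclusion.** The point holds as a moderate error of method. On Section 4.4's own SD, difference and ICC, 85% power at a true two-sided 5% level is not delivered with any number of schools that the protocol gives or implies. The reference distribution alone costs 4 to 5 points at 18 to 20 schools and about 8 at 12; the power of the planned layout is about 78% for 18 schools and 66% for 12. The figures assume equal school sizes, a comparison of school means, no covariate adjustment and schools − 2 degrees of freedom; using schools − 4 lowers them slightly and changes nothing in the conclusion. The conflict between 18 and 12 schools and the labelling of sigma as a mean are separate matters, and this point holds under either school count.

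**What to change.** In Section 4.4, replace the normal multipliers with t multipliers on (schools − 2) degrees of freedom, less any district terms, and restate the power for the school count finally confirmed: about 78% for 18 schools on the protocol's own SD, difference and ICC. If sigma is corrected first, recalculate from the corrected value.

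In Section 4.12, test the arm effects and form their confidence intervals against the same small-sample reference, so that the 5% level holds: t on school degrees of freedom with a bias-corrected GEE variance, or an analysis of school-level summaries.

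The cost is one recalculated, less favourable power figure, one sentence in 4.12 and slightly wider confidence intervals. No schools or pupils are added if the lower power is accepted. Keeping the 85% target is a different decision: it would need, for example, 24 schools with 80 analysed in each (1,920 pupils) or 18 schools with 130 (2,340).

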### **3.0. Literature review**

#### **Occurrence of dental caries, periodontal conditions and oral impacts on daily performance among adolescents**

Dental caries affect about 19-93.7% of adolescents globally and its distribution varies by demographic and social factors (Aldosari et al., 2004, Mtaya et al., 2009, Nurelhuda et al., 2009, Mashoto et al., 2010, Singh., 2011, Pakpour et al., 2011, Krisdapong et al., 2013, Al-Darwish et al., 2014, Mathur et al., 2014, Dye et al., 2015, Vernazza et al., 2016, Msyamboza et al., 2016, Lage et al., 2017, Borges et al., 2017, Giacaman et al., 2018, Simangwa et al., 2018, Simushi et al., 2018, Clark et al., 2019). The prevalence ranges from 41-72% in Europe and America (Jamelli et al., 2010, Dye et al., 2015, Lyra et al., 2015, Vernazza et al., 2016, Borges et al., 2017, Lage et al., 2017, Giacaman., 2018), 20.0-93.7% in Asia (Al-Sadhan, S., 2006, Pakpour et al., 2011, Krisdapong et al., 2013, Mathur et al., 2014, Al-Darwish et al., 2014,) and 8.8%- 50.98% in Africa (Nurelhuda et al., 2009, Mashoto et al., 2010, Singh., 2011, Msyamboza et al., 2016, Simagwa et al., 2018, Simushi et al., 2018). While some studies in Europe and America report no significant difference in caries occurrence by age and sex (Dye et al., 2015, Borges et al., 2017, Lage et al., 2017, Clark et al., 2019), others report significantly more girls than boys (Vernazza et al., 2016) and older than younger adolescents (Dye et al., 2015, Lyra et al., 2015) are affected. The disease also significantly affects more adolescents in rural than urban areas (Lyra et al., 2015, Borges et al., 2017, Giacaman., 2018) and those from larger than smaller family sizes (Lyra et al., 2015). In Africa and Asia, the disease affects significantly more girls than boys (Al-Sadhan, S., 2006, Al-Darwish et al., 2014, Msyamboza et al., 2016,), older than younger adolescents (Al-Darwish et al., 2014, Simagwa et al., 2018), and those from lower than higher socioeconomic status (Nurelhuda et al., 2009, Pakpour et al., 2011, Mathur et al., 2014, Krisdapong et al., 2013). The disease also affect significantly more urban than rural adolescents (Nurelhuda et al., 2009, Owino et al., 2010, Simushi et al., 2018), however Mashoto et al., (2010) and Mapengo et al., (2010) reported the opposite and Msyamboza et al., (2016) reported no difference.

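### Section 4.4 enters the mean DMFT as the standard deviation, so the sample size does not depend on the caries data and the stated 85% power rests on no variance estimate

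*Protocol*

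**What the plan says.** Protocol section 4.4 gives the total for two arms under simple random sampling as 2N = 4(Zα + Zβ)²σ²/δ². Its inputs are:

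- Zα, "estimated to be 1.96 for 95% Confidence Interval".
- Zβ, which "is value corresponding to 85% power of the study =1.03".
- σ, which "is known mean DMFT from a previous study in Ndola, Zambia", with the value 1.34.
- δ, which "is the expected clinically significant change in mean DMFT set at 20% =0.268".

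The text confirms that "2N is number of participants in two arms". The resulting 894 is multiplied by a design effect built on 80 pupils per cluster and an "Estimated intra-cluster correlation coefficient (ICC) to be 0.01". That gives 1,600, and a further 10% for loss to follow-up gives 1,760. The Summary and section 4.5 repeat 1,760. It is the protocol's only sample size calculation.

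**The concern.** In a comparison of two means, σ is the between-person SD of the outcome; it measures the noise against which δ must be seen. Section 4.4 puts the mean in that place and then defines δ as a fraction of the same mean. The Ndola figure looks like the empirical basis of the calculation but has no influence on the answer.

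Dental caries status is among the primary outcomes in section 4.10. Section 4.14 already concedes that 24 months is short for observing caries increment, so a null caries result is foreseeable. How such a result is read depends on the power claimed beforehand, and here that claim has no variance behind it.

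**Working it through.** **Inputs, all from section 4.4.** Zα = 1.96, Zβ = 1.03, σ = 1.34 (described as a mean), δ = 0.268 (20% of 1.34), cluster size m = 80, ICC = 0.01, loss 10%.

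**Reproducing the plan.**
- 2N = 4 × (1.96 + 1.03)² × 1.34² / 0.268² = 894.01.
- Design effect = 1 + (80 − 1) × 0.01 = 1.79, and 894 × 1.79 = 1,600.26.
- 1,600 × 1.10 = 1,760.

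The arithmetic is right. With the unrounded Zβ of 1.036 the first figure would be 898, a trivial difference. The fault lies in an input.

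**The mean cancels.** Let M be the mean, with σ = M and δ = 0.20M. Then σ/δ = 5 and 2N = 4 × 2.99² / 0.20² = 4 × 8.9401 × 25 = 894.01. Means of 0.5, 1, 1.34, 3 and 10 all return 894.01. The implied standardised effect is 0.20, which means SD = mean.

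**Power if the SD is something else.** After division by the design effect, 1,600 analysed pupils carry the information of 894 (1,600.26 / 1.79 = 894). With δ held at 0.268:

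Power = Φ(0.268 / (SD × √(4/894)) − 1.96), with √(4/894) = 0.0669.

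The protocol gives no SD, so the values below are assumptions on both sides of 1.34. The required total is 1,760 × (SD/1.34)², since N scales with SD².

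| Assumed SD | Basis | Power | Total needed to keep 85% |
|---|---|---|---|
| 1.005 | 0.75 × mean | 98% | 990 |
| 1.158 | √1.34, Poisson-like | 93% | 1,314 |
| 1.34 | equal to mean, as the plan implies | 85% | 1,760 |
| 1.66 | zero-truncated Poisson among the affected, 50.98% affected | 67% | 2,701 |
| 2.01 | 1.5 × mean | 51% | 3,961 |

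As a detectable difference at the plan's z values, 2.99 × SD × 0.0669 is 0.20 × SD: about 0.20 at SD 1.005, 0.27 at 1.34, 0.33 at 1.66 and 0.40 at 2.01.

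**What the protocol's own prevalence range implies.** The literature review (section 3.0, on occurrence) puts adolescent caries prevalence at "8.8%- 50.98% in Africa". If a proportion p is affected, the mean among the affected is 1.34/p, and the zeros alone force SD ≥ 1.34 × √((1 − p)/p). At p = 0.5098 this is 1.34 × √(0.4902/0.5098) = 1.31, and the floor rises as p falls: 1.64 at p = 0.40 and 2.05 at p = 0.30. At SD 1.31, power is Φ(3.06 − 1.96), about 86%. So if no more than 50.98% of these pupils are affected, power is at most about 86%, and lower once the affected pupils differ among themselves. Applying that range to this population is an assumption.

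**The case against.** **1.34 might be a mislabelled SD.** This does not rescue the text. δ is described as a 20% change in mean DMFT, and 0.268 is 20% of 1.34, so the same calculation uses 1.34 as the mean. One of the two definitions must change.

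**SD = mean is a possible value.** This stands. The floor of 1.31 at 50.98% affected lies close to 1.34, so the plan's number is not impossible. It is undeclared and unsourced.

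**A reader might infer that the trial is under-powered, or that 85% is probably overstated.** The documents do not establish this. They do not give the prevalence in the study that supplied 1.34, and the prevalence range comes from a multi-country review. Under the zero-truncated Poisson model, 65% affected would give an SD of 1.34 (85% power) and 70% affected an SD of 1.23 (90%). That a caries count usually has an SD above its mean is outside knowledge, which the protocol does not supply.

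**DMFT is not what the plan tests.** This also stands, and it widens the fix. Objective 4 (section 2.2 and Appendix 6) concerns caries prevalence. Caries is coded by CAST, and section 4.12 compares the groups by GEE with odds ratios. A correct SD of DMFT would still not give the power of that test, and the percentages above do not carry over to it.

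**The power figures borrow the plan's other inputs.** True. They hold for m = 80 and ICC 0.01. Section 4.5 expects clusters of 90 to 100, for which the design effect would be 1.89 to 1.99.

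**Conclusion.** Section 4.4 is wrong as written. A mean stands where an SD belongs, the mean cancels, and 894 (hence 1,600 and 1,760) would be the same for any caries level at the chosen 20% and z values. The stated 85% power therefore rests on no variance estimate.

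The size of the error is a range: about 98% down to 51% power for SDs from 1.005 to 2.01, given δ = 0.268, 1,600 analysed pupils and a design effect of 1.79. Its direction is open. The one conditional statement that the protocol's figures allow is a ceiling of about 86% if at most 50.98% of pupils are affected. The supportable conclusion is that 85% is unsupported, not that it is known to be too high.

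**What to change.** 1. Replace σ in section 4.4 by an SD of DMFT with its source, from the cited Ndola survey or this trial's baseline examination. Keep 1.34 only as the mean from which δ is derived.
2. Recompute, and state the power or the detectable difference of the existing 1,760.
3. State the same for caries prevalence compared by GEE odds ratio, using a baseline prevalence, since that is the test planned for objective 4.
4. Remove the 85% if it does not survive.

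The cost is one recalculation and possibly a less favourable stated power. Enrolment, intervention and follow-up stay as they are, provided that any lower power is accepted and reported. Holding 85% at a larger SD would need more pupils (about 3,961 at SD 2.01), which this fix does not ask for.

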### **2.2. Specific Objectives**

- 1 To determine prevalence and distribution of dental caries, periodontal conditions and oral impacts on daily performance among adolescents in Copperbelt Province, Zambia
- 2 To determine the association between dental caries and oral health related quality of life among adolescents in Copperbelt Province
- 3 To assess the effects of a six months modified basic package of oral care intervention on knowledge and behaviors related to dental caries after 18 and 24 months of follow up.
- 4 To assess the effects of a six months modified basic package of oral care intervention on prevalence of dental caries after 18 and 24 months of follow up
- 5 To assess the effects of a six months modified basic package of oral care intervention on prevalence of oral impacts on daily performance after 18 and 24 months of follow up

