#### **4.10. Study outcomes**

The expected primary outcomes are improved oral health (dental caries status and gingivitis) and OHRQoL. The secondary outcomes include improved oral hygiene (plaque score) and oral health knowledge and related behaviors. The effect sizes for improvement in oral health and oral health related quality of life are based on average improvement achieved in similar studies reviewed.

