#### **4.14. Study limitation and mitigation**

##### **Study limitations**

1. The follow up duration will be limited to 24 months which is enough to observe change in oral health related behaviors, plaque and bleeding but not reasonably enough for observing dental caries increment.
2. The study will follow single blind design where only the examiners will be blinded, the principal investigator and the participants will not be blinded due to the nature of the intervention which requires administration of educational technical materials and provision of treatment which cannot be easily concealed.
3. Adolescents may modify their oral health related behavior in response to awareness that there are being observed (Hawthorne effects).

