##### **Mitigation**

- 1 Dental caries assessment using CAST (Frencken *et al.*, 2011) will be used to capture incremental stages of dental caries development and dental caries variable will continue being followed up after 24 months.
- 2 The data analyst will be blinded during analysis stage to avoid subjective decisions on handling missing data, transforming variables, undertaking subgroup analysis, and selecting covariates due to prior knowledge of treatment allocation.
- 3 The interventions will end six months before the last follow up and therefore the effect of adolescents acting due to the reason that their being followed-up will be controlled in the data collected at the last follow up visit.

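### The 85% power in section 4.4 is for a difference in mean DMFT, which the trial does not analyse; caries prevalence by odds ratio and the other primary outcomes have no power figure

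*Protocol*

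**What the plan says.** Section 4.4 is the only sample size calculation in the protocol. It uses a two-sided 5% level ($Z_\alpha$ "estimated to be 1.96 for 95% Confidence Interval"), 85% power ($Z_\beta$ "is value corresponding to 85% power of the study =1.03") and an effect in mean DMFT that "is the expected clinically significant change in mean DMFT set at 20% =0.268".

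The outcome and analysis sections use a different measure. Section 2.2 sets objective 4 as the effect on "prevalence of dental caries after 18 and 24 months of follow up". The dependent-variable section codes caries by CAST and counts enamel change as caries. Section 4.12 summarises caries as number and percentage and says of the comparison between groups that "generalized estimating equations will be performed and reported in odds ratio and 95% confidence interval". Appendix 6 reports every intervention objective as number, percentage and odds ratio. Its time points for objective 4 differ from those in 2.2, but the outcome in both is prevalence.

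Section 4.10 names caries status, gingivitis and OHRQoL as primary. It says the effect sizes for oral health and OHRQoL are "based on average improvement achieved in similar studies reviewed", but gives none.

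Section 4.14 concedes that 24 months is enough to see change in behaviour, plaque and bleeding "but not reasonably enough for observing dental caries increment". Part of its mitigation is that the "dental caries variable will continue being followed up after 24 months".

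**The concern.** A power statement holds for one outcome, one contrast and one test. Here the sizing variable is a mean count of teeth, and the analysed variable is the proportion of adolescents with caries. The protocol itself fixes both, so this is not a detail waiting for a SAP. The power of a comparison of proportions depends on the control proportion and on the effect on that proportion. Neither follows from a mean DMFT of 1.34 or a 20% change in it.

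At stake is how the result is read. If the caries odds ratio is inconclusive, 4.4 invites the reader to set it against 85% power that was never calculated for it. For gingivitis and OHRQoL there is nothing to set the result against, although 4.10 implies that effect sizes were chosen.

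The mitigation in 4.14 has a related weakness. Table 1 and section 4.13 give the control group the whole package at the end of follow-up. Caries data collected after that no longer compare the package with its absence.

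**Working it through.** **The plan's own figure.** Inputs from 4.4: z values 1.96 and 1.03, σ = 1.34, δ = 0.268, ICC 0.01, cluster size 80, loss 10%.

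- 2N = 4(1.96 + 1.03)² × 1.34² / 0.268² = 894.01, so 894, or 447 per arm.
- Design effect = 1 + 79 × 0.01 = 1.79, and 894 × 1.79 = 1,600.26, so 1,600.
- 1,600 × 1.10 = 1,760.

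The figures reproduce. Power for mean DMFT at 447 per arm is Φ(0.268 / [1.34 × √(2/447)] − 1.96) = 84.8%. This takes 1.34 as the standard deviation, although 4.4 describes it as a mean.

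**The same sample applied to caries prevalence.** Effective n is 447 per arm, two-sided 5%:

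power = Φ( (p₁ − p₂) / √{[p₁(1 − p₁) + p₂(1 − p₂)] / 447} − 1.96 ), with p₂ = (1 − r) p₁.

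The control prevalence p₁ spans the African range in section 3.0, 8.8% to 50.98%. The relative fall r is an assumption in every row. The 20% borrows the figure that 4.4 sets for mean DMFT only. The 24% and 50% are the ends of the range that section 3.0 quotes for toothbrushing interventions, and 35% is the larger of its two health-education figures.

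Worked cell: p₁ = 0.40, r = 20%, p₂ = 0.32 (odds ratio 0.71). The standard error is √[(0.2400 + 0.2176)/447] = 0.0320. Then 0.08/0.0320 − 1.96 = 0.54, and Φ(0.54) = 71%.

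| Relative fall (assumed) | 8.8% | 20% | 30% | 40% | 51% |
|---|---|---|---|---|---|
| 20% | 16% | 34% | 53% | 71% | 87% |
| 24% | 22% | 47% | 69% | 86% | 96% |
| 35% | 43% | 81% | 96% | 99% | nearly 100% |
| 50% | 76% | 99% | nearly 100% | nearly 100% | nearly 100% |

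A pooled-variance version differs by less than one percentage point. If 10% of 1,760 are lost, 1,584 remain. Dividing by 1.79 gives 885 effective instead of 894, which also moves power by less than a point. Any gain from baseline or repeated measures in the GEE, and any loss from the small number of clusters, is left out.

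**OIDP, the OHRQoL measure.** Section 3.0 cites a 13.7% improvement after ART and OUT and does not say whether it is relative or in percentage points. Section 1.1 gives 35.6% to 54.6% prevalence of impacts in Sub-Saharan Africa. Using the 18 schools of section 4.5: 1,584/18 = 88 per school, design effect 1 + 87 × 0.01 = 1.87, and 1,584/1.87 = 847 effective in total.

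| Reading of 13.7% | Power at 35.6% | Power at 54.6% |
|---|---|---|
| Relative (p₂ = 0.863 p₁) | 33% | 59% |
| Percentage points (p₂ = p₁ − 0.137) | 99% | 98% |

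With 447 per arm instead, the relative reading gives 34% and 61%.

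**Gingivitis.** No effect size or power is stated, so there is nothing to reproduce.

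**The case against.** The strongest reply is that the sample may well be adequate for the real analysis, and that any low figure depends on choosing unfavourable inputs. Much of this stands.

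- The 20% fall in prevalence is not the protocol's figure; it sets 20% for mean DMFT alone. Section 3.0 cites reductions of 24% to 50% in the proportion with caries, and these give clearly higher power.
- The lowest prevalences fit poorly with the local mean DMFT of 1.34. At 8.8% prevalence that would be 1.34/0.088 = 15 affected teeth per affected adolescent; at 51% it is 1.34/0.51 = 2.6. Counting enamel lesions as caries pushes prevalence up further. The 16% is therefore an end of the range and not a sensible planning case.
- The protocol does not settle whether a tooth restored by ART still counts as caries, so treatment might itself lower prevalence.
- The short follow-up is disclosed in 4.14, and the use of CAST to capture early stages is a reasonable part of the mitigation.

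A reader might infer more than the documents support in two places. One is that the trial has only 16% to 71% power for caries. That range needs the borrowed 20% fall and a prevalence of 40% or less, while the cited African range runs to 50.98%, where the same fall gives 87%. The other is that a 0.268 difference in mean DMFT is out of reach in 24 months. Testing that needs a control-group increment, which the protocol does not give.

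None of this restores the 85%. That power moves from 16% to nearly 100% across the protocol's own literature ranges and the borrowed 20% is the reason a prevalence and an effect must be stated.

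**Conclusion.** The point holds as a mismatch between the sizing variable and the analysed variable. It rests on the protocol's text and needs no outside figure. The 85% belongs to a comparison of mean DMFT that is not planned. The planned comparison of caries prevalence has no stated power, and neither has gingivitis or OHRQoL.

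The size of the consequence is open. It depends on control prevalence, on relative effect and, for OIDP, on how the cited 13.7% is read (33% to 59%, or 98% to 99%). All these figures take the protocol's ICC of 0.01 as given. The OIDP figures also assume 18 schools, whereas section 4.7 describes four per district. Confidence is high for the mismatch. No single cell of the tables should be quoted as the trial's power.

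The statement in 4.14 about caries follow-up after 24 months is a smaller, related fault: it cannot extend the randomised comparison once controls have had the package.

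**What to change.** - **Section 4.4.** Keep 1,760. Replace the mean-DMFT power statement with the power, or the detectable odds ratio, for each primary outcome as it will be analysed. State the control prevalence and effect size used, and add a sensitivity range like the tables above.
- **Section 4.10.** Give the effect sizes it says were taken from similar studies, and say whether each is relative or in percentage points.
- **Section 4.14.** State that 24 months is the last comparison with controls who have not had the package. Later caries follow-up may be kept as descriptive, but not as mitigation for the randomised comparison.

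Changing objective 4 to a count of new lesions is not a ready alternative, because 4.14 itself says 24 months is too short to observe caries increment.

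The cost is a recalculation and new wording in three sections. The stated power may turn out less favourable than 85%. No extra participants are needed.
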